**2. OBJECTIVES AND ENDPOINTS**

Primary objective and primary endpoint

The primary objective of the study is to show that PTBD is not inferior to EUCD in terms of technical success rate. The technical success rate is defined as the successful implantation of a metal stent into the bile duct system (= successful drainage of the contrast medium via the metal stent within one minute after injection).

The primarily technical success of the intervention is decisive for the further procedure following the examination (reintervention necessary ? surgery necessary ?) and is presumably almost identical to the clinical success of the intervention, which can only be verified after 7 days (drop in bilirubin value ≥ 50%). The technical success rate was therefore preferred to the clinical success rate as the primary endpoint.

In PTBD there is only one possibility of metal stenosis insertion across the tumor stenosis in the common bile duct (blunt). In EUCD, the additional option of transluminal stent placement in the context of EUS-HGS or EUS-CDS remains.

The prompt (1 week) implantation of a metal stent after the application of an external drainage in PTBD is also considered a technical success. However, the application of an external drainage is counted as "reinvention".

Secondary objectives and secondary endpoints

In addition to the technical success rate, both interventions will be compared descriptively with regard to other endpoints. All endpoints or points in time refer to the technically successful intervention.

1. Clinical success rate of bile extraction, defined as reduction of the bilirubin value of ≥ 50% 7 days after technically successful intervention in relation to the baseline value before intervention.

2. The occurrence of at least one complication (including death) within 30 days (description + count)

3. Duration of bile duct intervention (PTBD/EUCD) in minutes

- for PTBD: from the application of the local anaesthetic to the application of the skin dressing

- for the EUCD: from the insertion of the endoscope to the removal of the endoscope

4. Post-interventional pain sensation on day 1 and day 7 after intervention (in relation to baseline before intervention): visual analogue scale

5. Length of hospital stay (from the day of the first intervention to the day of discharge) in days

6. Number of re-interventions between the first intervention and the end of the follow-up

(n) after 6 months.

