5.4 Co-interventions

After the clinically successful intervention on the bile duct (decrease of the bilirubin value), palliative chemotherapy can be performed depending on the underlying malignant disease. The respective chemotherapy is specified in the documentation. Palliative chemotherapy can influence the rate of reintervention (usually reduction of the rate of reintervention), disease-specific survival (usually prolongation) and overall survival (usually prolongation). This is taken into account in the evaluation of the data.

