**8. ASSESSMENT OF PATIENT SAFETY**

8.1 Definition and documentation of complications

In the study population with advanced oncological diseases, numerous tumour- and tumour therapy-related adverse events are to be expected.

For the assessment of patient safety with regard to the interventions performed in the study, only certain adverse events in terms of potential complications of PTBD/EUCD, of which a major part is to be expected within a period of 30 days after the intervention, are of interest and complications are to be documented in the notification form.

The following potential complications of PTBD and/or EUCD are recorded in the CRF with date and severity (mild, moderate, severe, fatal) (see Table 1, below) (multiple entries possible):

- Bleeding/haematoma

- Haemobilia

- intra-abdominal bile leakage

- Pneumothorax

- Biliary pleural effusion

- Pneumoperitoneum

- Perforation of the gastrointestinal tract

- Therapy-relevant (cholangial-)sepsis

- Newly occurring cholangitis (see comment below)

- Abscess

- Purulent peritonitis

- Cholecystitis

- Metal stent dysfunction/migration

- Other (description in free text)

To be distinguished from the above mentioned complications and not to be recorded:

- metal stent-closure caused by the ingrowth of tumour tissue or by choledocholithiasis

- Adverse events associated with anaesthesia and/or sedation

- Adverse events associated with chemotherapy

- Cholangitis as a possible complication of the intervention by PTBD or EUCD requires a special consideration: Only the newly appeared and not the pre-existing cholangitis is considered a complication ! Since the patients are treated peri-procedurally prophylactically with antibiotics, cholangitis is only considered a complication if an intensification of antibiotic therapy becomes necessary and the cholangitis can be safely attributed to the intervention !

- Postinterventional pain (will be collected separately)

Severity of the complication

Table 1: Severity of complications according to the recommendations of the American Society for Gastrointestinal Endoscopy (ASGE) (16,17)

| **Severity of the complication** | **Slightly** | **Moderate** | **Severe** | **Fatal** |
| --- | --- | --- | --- | --- |
| Procedure aborted or not yet started because of UE | x |  |  |  |
| Unscheduled anesthesiological measure required in connection with a procedural adverse event (e.g. endotracheal intubation) |  | x |  |  |

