8.2 Causal link between intervention and complication

As a rule, the connection or non-connection of a complication with the intervention performed is obvious. Nevertheless, a distinction is made between safe, probable and unlikely.

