9.2 Statistical evaluation

The primary endpoint is the technical success rate in malignant distal choledochial stenosis using a self-expanding metal stent. The non-inferiority of PTBD compared to EUCD shall be demonstrated. The corresponding test hypothesis is

H0: pEUCD - pPTBD ≥ δ vs. H1: pEUCD - pPTBD < δ

Where pPTBD describes the technical success rate in the EUCD group, pPTBD the technical success rate in the PTBD group and δ=0.1 the non-inferiority limit.

The non-inferiority of PTBD to EUCD is verified by the Farrington/Manning test with a one-sided significance level of 2.5%.

Since this is a non-inferiority study, the primary evaluation will be based on both the Intention-To-Treat (ITT) Set and the Per-Protocol (PP) Set. In the ITT set, all patients are considered in whom the intervention was performed, even if it was technically unsuccessful or participation in the study was terminated prematurely. If the intervention has to be terminated prematurely (e.g. due to organ perforation), this patient is included in the primary evaluation. The primary evaluation is based on the assumption of technical failure in these patients.

In the PP Set, only those patients are included in the evaluation for whom the intervention was performed and the technical success was measured.

In sensitivity analyses, best case and worst case scenarios are calculated for the missing values. In addition, regression models are planned to investigate the influence of confounders on the endpoints. The variables intervention (EUCD with subgroups or PTBD with side localisation), BMI or bilirubin value are considered as input variables in the baseline study. The binary outcome variable is the technical success of the intervention. The affiliation of the individual patients to the two evaluation collectives is defined in SAP before the database is closed.

If non-inferiority can be shown with regard to the technical success rate, the occurrence of at least one complication (expected complication rate for both interventions: 10-20%) is compared hierarchically in the next step and tested for differences between the groups (based on the ITT set). Due to the hierarchical approach, the full level alpha, in this case two-sided 5%, is tested.

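### Section 8.1 does not say whether a listed complication ascribed to chemotherapy is still recorded, so non-serious events can be lost irrecoverably from the 30-day complication test

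*Protocol*

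**What the plan says.** Protocol section 8.1 gives a list of potential complications of either procedure to be entered in the CRF with date and severity. It includes bleeding, abscess, "Therapy-relevant (cholangial-)sepsis" and an open category for other events. A second list follows under the words "To be distinguished from the above mentioned complications and not to be recorded", and one of its bullets is "Adverse events associated with chemotherapy". The section gives no criterion for the attribution to chemotherapy, no time window, no adjudication, and no rule for an event that fits both lists.

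Cholangitis is treated separately in the same section. It counts only if antibiotic treatment has to be intensified and "the cholangitis can be safely attributed to the intervention".

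Section 8.2 grades the causal link of complications: "Nevertheless, a distinction is made between safe, probable and unlikely".

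Section 2 defines the endpoint as "The occurrence of at least one complication (including death) within 30 days". Section 9.2 makes it the second step of the hierarchy: once non-inferiority is shown, "the occurrence of at least one complication (expected complication rate for both interventions: 10-20%) is compared hierarchically in the next step", at two-sided 5%.

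Section 5.4 says that, once the intervention has been clinically successful, "palliative chemotherapy can be performed depending on the underlying malignant disease". Section 7.2.2 judges clinical success at day 7.

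**The concern.** Suppose a patient has a septic episode or a bleed on day 20, after starting chemotherapy. The event is on the list of complications, and it can also be called an adverse event of chemotherapy. The investigator decides which list applies before anything is written down. If the second list is chosen, the complication form stays empty. A statistical analysis plan cannot repair this, because the observation was never captured.

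Three features of the design make this matter. The endpoint is alpha-controlled. Physicians, patients and study nurses are unblinded (section 5.3). Each centre performs only one of the two techniques (section 4.2), so attribution habits cannot be compared between techniques within a centre. Section 8.1 itself opens by expecting many events due to the tumour and its treatment, so the overlap is foreseeable.

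**Working it through.** **Which events are exposed.** Setting the provisions side by side:

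- *Death*: named in the endpoint (section 2), so not exposed in the same way.
- *Serious events*: section 4.6.2 defines a serious adverse event as any adverse event with one of the listed consequences, whatever its link to the intervention. Section 8.4 ties the definition to the serious or fatal complications of section 8.1, so an event removed from 8.1 may fall outside it. Neither section says that these forms feed the complication count.
- *Non-serious listed events*: for example, those that lead to a transfusion, a repeat endoscopy or a readmission of 4 to 10 days (the moderate grade in the severity table). None of these is a criterion for a serious adverse event. This is the real gap.
- *Cholangitis*: has its own attribution rule, so the chemotherapy bullet adds little.
- *Pneumothorax, bile leakage and similar events*: hardly ascribable to chemotherapy. Sepsis, bleeding and abscess carry the point.
- *Timing*: sections 5.4 and 7.2.2 together suggest that the bullet acts mainly from about day 7 to day 30.

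**Consistency with section 8.2.** The scale runs down to an unlikely link, so a complication probably not due to the procedure is still recorded and then graded. The chemotherapy bullet reverses that order: cause is judged first, and recording depends on it.

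**Illustration of size.** Inputs from the protocol: 106 patients per arm (section 9.1), expected complication rate 10-20%, two-sided 5% (section 9.2). Expected patients with a complication per arm: 106 × 0.10 = 10.6 to 106 × 0.20 = 21.2. The protocol gives no figure for the share lost, so the losses below are assumptions. The protocol does not name the test; a pooled two-proportion z-test is also assumed.

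Rejection probability, normal approximation, with d = p1 − p2, p̄ = (p1 + p2)/2, SE0 = √[2p̄(1 − p̄)/n], SE1 = √[(p1(1 − p1) + p2(1 − p2))/n]:

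Φ((d − 1.96·SE0)/SE1) + Φ((−d − 1.96·SE0)/SE1)

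True rate 15% in both arms, 3 points lost in one arm only (3% of 106, about 3 patients), so recorded rates are 15% and 12%:

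- p̄ = 0.135, SE0 = 0.0469, SE1 = 0.0469, 1.96·SE0 = 0.0920
- (0.03 − 0.0920)/0.0469 = −1.32, Φ = 0.093
- (−0.03 − 0.0920)/0.0469 = −2.60, Φ = 0.005
- sum 0.098

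Exact enumeration of the same test at 106 per arm:

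| Recorded rates | Assumed loss in one arm | Rejection probability |
|---|---|---|
| 15% / 15% | none | 0.051 |
| 15% / 14% | 1 point (about 1 patient) | 0.056 |
| 15% / 13.5% | 1.5 points | 0.063 |
| 15% / 12% | 3 points (about 3 patients) | 0.100 |

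If the true rates differ, at 20% and 10%, power is 0.542. With 2 points lost in the worse arm only (18% and 10%) it is 0.396.

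A loss of 3 points from 15% is one fifth of that arm's events. What matters for the false-positive rate is the difference in loss between the arms, not the gross loss.

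**The case against.** The strongest reply is that the second list is set apart from the listed complications, and that section 8.1 explains why: many events of tumour and tumour treatment are expected, and only complications of the two procedures are of interest. On that reading the bullet keeps ordinary chemotherapy toxicity off the form, and a listed complication is recorded regardless. This is a fair reading, but the text does not state it. Two centres could apply the section differently without breaching it. The CRF filling instructions mentioned in section 10.1 might settle the matter, but they are not shown.

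A second reply is that other routes exist: adverse events are asked about at each contact (section 7.1), documented up to discharge (section 6.4), and evaluated in addition to the secondary endpoints (section 9.2). This stands in part. A reader might infer that such events leave no record at all; the documents do not support that for serious or fatal events. For non-serious listed events, section 8.1 tells the investigator not to record them.

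A reader might also infer that the exclusion is open only in patients already drained successfully. Section 5.4 places chemotherapy after success but does not bar it before or around the intervention, so this is an inference. Nor does the protocol predict different access to chemotherapy by arm: it plans for 95% technical success in both and presumes clinical success to be almost identical to technical success.

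Finally, centre is not the same thing as arm. Five centres are nested in each arm, and their habits partly average out. And because the endpoint counts patients with at least one complication, a patient with another recorded complication still counts.

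**Conclusion.** The point holds as a recording ambiguity with a confirmatory consequence. Section 8.1 does not say which list prevails, so a listed, non-serious sepsis, bleed or abscess can be left off the complication form on an unblinded judgement and cannot be recovered for the 30-day test.

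The documents do not show that a bias exists, or which arm it would favour. The rise in the false-positive rate from 5% to 10% rests on an assumed loss of 3 points in one arm and none in the other, and on every lost event being one that should have counted. With a loss of 1 point the rate is 5.6%, which is negligible. Leaving out events that chemotherapy truly caused is correct for a procedural endpoint; the fault is that this cannot be checked afterwards. The primary endpoint and its sample size are not affected.

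**What to change.** In section 8.1, limit the chemotherapy bullet to events that are not on the list of complications. Record every listed event within 30 days whatever its presumed cause, grade it on the section 8.2 scale, and tick whether chemotherapy had started before the event.

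Prespecify whether the main complication analysis counts listed events ascribed to chemotherapy, and report the other version as a sensitivity analysis. This is a real choice. Counting them removes the investigator's attribution from the main result but brings some chemotherapy-caused events into a comparison of procedures, which could count against an arm whose patients start chemotherapy sooner. Leaving them out keeps the endpoint procedural but dependent on unblinded attribution. Once the events are recorded, both versions can be shown.

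The cost is one reworded line, one tick box and a few more recorded events.

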5.3 Randomisation and blinding

Randomisation is not carried out, as one centre cannot usually offer both interventions (PTBD and EUCD) of the same high quality due to the complexity and experience required. Therefore, each centre offers the respective standard method (EUCD or PTBD). At least 10 study centres will participate in the study. When selecting the centres, care is taken to ensure that both university hospitals and non-university institutions are selected for both groups. All potentially eligible patients will be screened (see Chapter 6.1) and, if suitable, informed about the study. It is assumed that the recruited patients of both groups have similar characteristics and are comparable. Possible differences in patient characteristics are taken into account in the data evaluation. However, it is not expected that different patient characteristics (e.g. pancreatic carcinoma and bile duct obstruction versus LK metastasis in liver hilus with bile duct obstruction) will have a relevant influence on the success or failure of the intervention.

Due to the nature of the interventions, the attending physician cannot be blinded. Since only one of the two surgical techniques is used in a centre, the patient and study nurses cannot be blinded either. With the exception of the secondary endpoint of pain perception, the endpoints, especially the primary endpoint, are objectively measurable outcomes. Therefore, it is assumed here that there is little room for influence and that the risk of bias is low. The biometrician has no access to the data until after the database has been closed.

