5.6 Pre- and concomitant diseases

Pre- and concomitant diseases besides the underlying malignant disease that are present at the time of informed consent are not documented, as they are not expected to have a relevant impact on key endpoints of the study such as the technical and/or clinical success rate or the occurrence of complications of the intervention. By differentiating between Overall Survival and Disease Specific Survival, it is possible to specify the proportion of disease-specific causes (related to the underlying malignant disease causing the biliary obstruction) in the death of patients. It is expected that the underlying malignant disease is the main life-limiting factor in the observation period.

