6.2 Baseline visit

Facts of the clinical picture are documented (Case Report Form,p.3) . Cause of malignant bile duct obstruction, date of first diagnosis of the malignant underlying disease, cause of unsuccessful or for anatomical reasons not feasible ERCP.

The bilirubin value in mg/dl as an expression of the bile duct obstruction or cholestasis is measured and noted. The baseline visit should be performed the day before the intervention. Depending on the timing within the centre, baseline visit can be on the same day as screening visit if the intervention is scheduled for the following day.

Data that are documented as part of the study:

Demographics

- Gender

- Age

- Size

- Weight

Cause of the malignant bile duct obstruction (no multiple answers)

- Pancreatic carcinoma

- Distal bile duct carcinoma or extrahepatic bile duct carcinoma (Bismuth I)

- Gall bladder carcinoma

- Stomach cancer

- Duodenal carcinoma

- Papillary carcinoma

- Metastasis of another malign disease

- Other cause

Date of first diagnosis of the underlying malignant disease

Cause of unsuccessful or for anatomical reasons not feasible ERCP (no multiple answers)

- Gastric outlet stenosis/duodenal stenosis (tumour-related or benign cause)

- Difficult to probe the optic disc using ERCP

- For (partial) gastrectomy

- Biliodigestive anastomosis

- Following bariatric surgery

- Other cause

Laboratory chemical result of bilirubin determination (in g/dl) Pain intensity on the visual analogue scale (0-10)

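### Whether cholangitis counts as a complication depends on its presence before the procedure, which the protocol does not record, so the complication comparison cannot be checked or adjusted for it

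*Protocol*

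**What the plan says.** Section 8.1 lists new cholangitis among the recorded complications and restricts it: "Only the newly appeared and not the pre-existing cholangitis is considered a complication". Because all patients receive antibiotic prophylaxis, it adds two further conditions: "cholangitis is only considered a complication if an intensification of antibiotic therapy becomes necessary and the cholangitis can be safely attributed to the intervention". Sepsis is on the same list ("Therapy-relevant (cholangial-)sepsis"), as is abscess, and neither carries a condition that it be new.

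Section 5.6 states: "Pre- and concomitant diseases besides the underlying malignant disease that are present at the time of informed consent are not documented". Its reason is that no relevant effect is expected on endpoints such as the "technical and/or clinical success rate or the occurrence of complications of the intervention".

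Section 6.2 lists the baseline data: demographics, cause of the obstruction, date of first diagnosis, reason why ERCP failed or was not feasible, bilirubin and pain score. Cholangitis, fever, inflammatory markers and current antibiotics are not on the list. Section 4.5 does not exclude patients with cholangitis.

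Section 9.2 tests the occurrence of at least one complication at two-sided 5% once non-inferiority for technical success is shown. It expects 10-20% in each arm. Section 5.3 has each centre use one technique, without blinding, and undertakes to take differences in patient characteristics into account in the evaluation.

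**The concern.** The counting rule in 8.1 needs a fact that 5.6 and 6.2 do not collect. The reason given in 5.6 also conflicts with 8.1: for cholangitis, the pre-existing condition decides by definition whether a complication is recorded.

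Pre-existing cholangitis is foreseeable here. Every patient enters with a clinically relevant bile duct stenosis and raised bilirubin (4.4), and 5.5 itself names cholangitis as a sign of an occluded duct.

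The endpoint affected is the only one after the primary that is tested at full alpha. Section 5.3 calls all endpoints except pain objectively measurable, but the step from cholangitis to new cholangitis is a judgement by a team that knows the technique, in a trial whose section 9.2 states which arm is expected to have fewer complications. Without randomisation, the share with cholangitis at entry may differ between the two sets of centres. The undertaking in 5.3 to account for patient characteristics cannot be kept for a characteristic that is not in the data. An analysis plan written later cannot repair this.

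**Working it through.** **Text check.**

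| Step | Needed to apply 8.1 | What the protocol collects |
| --- | --- | --- |
| Is the episode new? | Cholangitis status before the procedure | Not listed in 6.2; general non-documentation rule in 5.6 |
| Was antibiotic therapy intensified? | Regimen before the episode | No antibiotic item in 6.2 |
| Is it attributable to the intervention? | Site judgement | Judged by the treating site, unblinded |
| Can arms be compared at equal baseline status? | Baseline status by arm | Not available; the regression variables in 9.2 are intervention, BMI or bilirubin, with technical success as the outcome |

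**Can a direction or size be derived?** The protocol has no figure for cholangitis to reproduce. Its only related figures are 10-20% expected complications and 106 patients per arm, that is 106 × 0.10 = 10.6 to 106 × 0.20 = 21.2 patients with a complication.

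Let s be the share of an arm with cholangitis at entry, a the recorded complication rate in patients without it, and b the rate in patients with it, both equal across arms so that the techniques do not differ.

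- Recorded rate in an arm = (1 − s)·a + s·b
- Spurious gap, arm 2 minus arm 1 = (s2 − s1)·(b − a)

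The sign is that of b − a when s2 > s1. The protocol fixes none of s1, s2, a or b. To show what this means, assume new cholangitis 8%, other complications 12%, independent, and s1 = 10%, s2 = 30%. Then a = 1 − 0.92 × 0.88 = 0.1904.

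| Assumption about patients with cholangitis at entry | b | Gap = 0.20 × (b − a) |
| --- | --- | --- |
| Never have a counted new episode; other risk equal | 0.12 | −1.4 points (about 1.5 of 106 patients) |
| Same chance of a counted new episode; other risk equal | 0.1904 | 0 |
| Never have a counted new episode; other risk doubled | 0.24 | +1.0 point (about 1.1 of 106 patients) |

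Between the first and third rows the sign changes where the other risk is 0.1904 / 0.12 = 1.59 times as high.

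Over wider assumptions (new cholangitis 5-10%, other complications 10-15%, shares at entry from 10% v 30% to 0% v 50%), the first row runs from −0.85 points (0.20 × (0.15 − 0.1925)) to −4.5 points (0.50 × (0.10 − 0.19)). The third row runs from +0.2 points (0.20 × (0.20 − 0.19)) to +5.4 points (0.50 × (0.30 − 0.1925)). These are illustrations of the sign, not estimates.

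**The case against.** Several points on the other side have weight.

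- **The status may be recoverable.** Complications are entered with a date, adverse events are asked about at each contact (7.1), source data are archived (10.3) and monitors may inspect them (12.1). So it would be wrong to say that the classification can never be verified. What stands is that the status is not in the listed trial data, which is what the biometrician receives.
- **The case report form and the visit figure are not shown.** An item could exist there. But 10.1 says the forms are developed to this protocol, and neither 6.2 nor 5.6 provides for one.
- **Section 5.6 may not be meant to cover cholangitis** that arises from the malignant obstruction. That is arguable, and the text describes a practice of not documenting, not a ban. The gap in 6.2 remains on either reading.
- **The two further conditions in 8.1 give a working test.** They help, but neither records what was present beforehand.
- **The test is reached only after non-inferiority**, and cholangitis is one component of a composite. This limits the weight of the point.

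A reader might go further and infer that a patient with cholangitis at entry can never contribute an event, so that the arm with more such patients must show fewer complications. The text does not support this. Section 8.1 excludes the pre-existing episode, not the patient; a fresh episode within the 30-day window can still count. Sepsis and abscess count without a condition of being new, and an old cholangitis taken for a new one pushes the rate up.

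**Conclusion.** The point holds as a gap in data collection that affects a confirmatory comparison. Section 8.1 relies on a baseline status that 5.6 and 6.2 do not provide, and the reason given in 5.6 does not hold for cholangitis. An imbalance at entry between centre-allocated arms could be neither detected nor adjusted for from the trial data.

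The size and direction of any resulting bias are unknown. No prevalence, imbalance or cholangitis rate is given, and the sign turns on assumptions that the protocol does not settle. The conclusion rests on the data list in 6.2 being complete. The primary endpoint is not affected. The change is worth making because it is cheap and has to be made while data are collected.

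**What to change.** 1. **Section 6.2:** add a yes/no item, *cholangitis present immediately before the intervention*. The baseline visit is usually the day before, so the answer should be confirmed at the start of the procedure.
2. **Section 5.6:** name this item as an exception to the rule that existing conditions are not documented.
3. **Section 8.1:** refer to the item when an episode is classed as new or pre-existing, and state that a patient with cholangitis at entry can still contribute a later new episode. Defining new as absent at baseline would remove such patients from being counted and create the distortion that the item is meant to reveal.
4. **Section 9.2:** add a sensitivity analysis of the at-least-one-complication endpoint, adjusted for or stratified by the item, and report the item by arm.

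The cost is one tick on the case report form, taken from the routine work-up that sites already need in order to apply 8.1, a sentence each in 5.6 and 8.1, and one extra analysis. Treatment, eligibility and sample size are unchanged.
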